#### Treatment satisfaction

Treatment satisfaction is assessed using a self-developed questionnaire, consisting of five items. Each question is scored on a Likert-type scale from 1 to 4. The questionnaire addresses overall service satisfaction; i.e. satisfaction with treatment, recommendation of treatment, satisfaction about effectiveness of treatment and willingness to repeat treatment if needed. This questionnaire is shown in Additional file 1.

#### Health status

General health status is assessed with the EuroQol (EQ-5D), which is a validated self-administered questionnaire that contains a descriptive section and a valuation section. The descriptive section consists of five dimensions: mobility, self-care, usual activities, pain/discomfort and anxiety/depression. Each of these five dimensions has three levels of severity: no problems, some/moderate problems and extreme problems. Values of the five dimensions are linearly transformed into one single score, ranging from 0 to 1 (lower scores represent more problems). The valuation section of the EQ-5D contains a visual analogue scale; this vertical visual scale ranges between ‘best imaginable health state = perfect health’ (score of 100) and ‘worst imaginable health state = death’ (score of 0). The EQ-5D valuation section has been shown to be efficient and easy to use [62].

#### Functional impairment and activity limitations

Functional impairment and activity limitations are assessed using the 12-item self-report World Health Organization Disability Assessment Schedule 2.0 (WHODAS 2.0). The WHODAS 2.0 is based on the conceptual framework of the International Classification of Functioning, Disability and Health (ICF). It provides a global measure of disability and 7 domain-specific scores. It assesses health and disability on six dimensions, namely cognition, mobility, self-care, getting along, life activities and participation. WHODAS 2.0 has been validated in 1119 patients across 7 European centers with 13 chronic conditions and it has been shown to have good metric properties [63]

#### Daily activities

Daily activities are assessed using part of the Health Questionnaire of the Utrecht Health project [64] This part of the questionnaire assesses daily activity level during a regular week in the past months, i.e. the kind and duration of these activities. The blended care treatment focuses on activating participants, by increasing their potential pleasurable activities. By assessing daily activities we study a potential prognostic mediating factor in the recovery of depression.

#### Ecological momentary assessment (EMA)

We will capture real-time momentary ratings of cognitions as well as affect and emotions with so-called Ecological Momentary Assessment (EMA). Compared to conventional questionnaires, potential advantages of prospective precise measurement with EMA are less recall bias and increased detection of vulnerable patients with adverse disease trajectories [65].

Specifically, using a smart phone application called ‘DE Free’ ([name], used software TEMPEST, Batalas & Markopoulos) (Fig. 2), auditory cue signals will be sent to participants’ cellphones. Thereupon, participants will be asked to rate their momentary states. These include an appraisal of positive affect (i.e. being cheerful, content, and energetic) and negative affect (i.e. feeling gloomy, nervous, insecure, lonely, irritated, helpless, and guilty), and activity levels (i.e. being active, pleasantness of activity, and energy involved in performing activity). Momentary states are rated on visual analogue scales, which are either numerical and ranging from 0 to 100 or ordinal and ranging from e.g. “not at all” to “very much”. Furthermore, participants will be asked to indicate the specific activities they were undertaking and the specific situation they were in while rating these momentary states (e.g. being at home and doing household chores). Participants will be asked to rate their momentary states in the following time schedule: every other day, 5 times per day, over the course of a 10-week period. Auditory signals will be sent at random moments during the following time intervals: equally spread between 8.30 a.m. and 7.30 p.m.

**Fig. 1 Fig1:**
[figure not shown]
Outline of inclusion, baseline assessment, and randomization and follow-up assessmentsGP: general practitioner. SCID-I: Structured Clinical Interview for DSM disorders. HRSD-17: Hamilton Rating Scale for Depression, 17 items. EMA: ecological momentary assessments. QIDS-16: quick inventory of depressive symptomatology, 16 items. WHODAS-II: WHO Disability Schedule 2.0. EQ-5D: EuroQol five dimensions questionnaire. TIC-P: Trimbos and iMTA questionnaire on Costs associated with Psychiatric illness

**Fig. 2 Fig2:**
[figure not shown]
Screenshot from the ‘DE-free’ application

### Resource use

#### Costs related to the intervention

To calculate costs related to the internet treatment, we include costs of running the website platform and costs of the guidance by the GP or MHW.

#### Direct and indirect costs

We will measure health care costs in general (direct costs) as well as productivity losses (indirect costs) with the revised version of the Trimbos and iMTA Questionnaires on Costs Associated with Psychiatric Illness (TiC-P) [66, 67]. Direct costs are measured by investigating, which contact with health professionals has occurred and which type of medication has been prescribed. Indirect costs are measured by work absenteeism and reduced productivity. The TiC-P questions cover the previous six months; it is administrated at 6 and 12 months follow-up.

### Sample size

The sample size is based on demonstrating non-inferiority of blended care compared to usual care for the primary outcome, i.e. the reduction on HRSD-17 from baseline to three months follow-up. An acceptable non-inferiority margin has been defined as the maximum clinically irrelevant difference between treatments [68]. The non-inferiority margin is set to be the half of minimal clinical important difference of 3 points on the HRSD-17 scale as advised by the FDA [60, 69, 70]; i.e. a non-inferiority margin of 1.5 points at the HRSD-17 (0.31 SD). The sample size was calculated with one-sided t-test with a power of 80% (α = 0.025) to detect a non-inferiority margin of 1.5. We compensated for an expected loss to follow-up of 20%. We adjusted for covariance, as advised to reduce required sample sizes and costs [71, 72]. In this correction we assumed a correlation coefficient (ρ) of 0.5, as recommended when the correlation coefficient is unknown [71, 73]. The number of participants needed is then corrected with design factor (1 − *ρ*
^2^), where ρ is the correlation coefficient. This resulted in a calculated design factor of 0.75. The final number calculated necessary to complete the trial is 151 participants per condition (a total of *N* = 302).

### Additional analysis

#### Economic outcomes

The cost-effectiveness and cost-utility of blended care will be studied from a societal perspective, using a time horizon of 12 months. To determine the cost-effectiveness of both treatments, we will estimate costs in both treatment groups. To calculate the total direct medical costs we will estimate the resource use. The resource use will be valued according to the Dutch guidelines for cost studies [67]. Costs of blended care will be estimated by true resources used. Medication use will be valued based on costs a provided by The National Health Care Institute (Zorginstituut Nederland, ZIN). Total costs for both interventions will be summed-up over the 12-month study period. An incremental cost effectiveness ratio (ICER) will be calculated using the primary measure of effect: HDRS-17. In addition, a secondary analysis will be performed using the number of patients with a response as defined under secondary outcomes. In order to be able to compare the effects of blended care to other health care interventions, also a cost-utility analysis will be done; using EQ-5D defined utilities. Bootstrapping will be performed to depict the 95% confidence intervals surrounding the cost effectiveness, and cost utility ratios. Cost-effectiveness planes will be plotted in order to represent the cost-effectiveness graphically.

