### Outcomes

#### Primary outcome

The primary outcome is the reduction of depressive symptoms from baseline to three months follow-up, as measured with the Hamilton Depression Scale 17-items (HRSD-17) [58–60]. This is a clinician-rated scale consisting of 17 items. This scale has been widely used in clinical trials and serves as gold standard for assessment of depression. It has been found valid and reliable measurement outcome with a higher inter-rater reliability and test-retest reliability [59, 61].

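### Bootstrap 95% intervals are planned on the cost-effectiveness ratios themselves, which have no clear meaning in the zero-difference scenario that the sample size implies, and the effect time point of the ratio is not stated

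*Protocol article*

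**What the plan says.** Under Economic outcomes the protocol article takes a societal perspective "using a time horizon of 12 months" and sums costs over the 12-month study. On the effect side: "An incremental cost effectiveness ratio (ICER) will be calculated using the primary measure of effect: HDRS-17". A second analysis uses the number of responders, and a cost-utility analysis uses EQ-5D utilities. Uncertainty is handled in one sentence, "Bootstrapping will be performed to depict the 95% confidence intervals surrounding the cost effectiveness, and cost utility ratios", followed by a plan to plot cost-effectiveness planes. Neither net benefit nor an acceptability curve is mentioned.

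Two other sections bear on this. Under Sample size: "The sample size is based on demonstrating non-inferiority of blended care compared to usual care for the primary outcome", and "The sample size was calculated with one-sided t-test with a power of 80% (α = 0.025) to detect a non-inferiority margin of 1.5". Under Primary outcome: "The primary outcome is the reduction of depressive symptoms from baseline to three months follow-up". The HRSD-17 is also measured at 12 months (Table 1), its 12-month reduction is a secondary outcome, and response is defined at both 3 and 12 months.

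**The concern.** An ICER is a cost difference divided by an effect difference. When the effect difference may be zero, the ratio misbehaves. Replicates with an effect just above zero and just below zero give very large ratios of opposite sign. A negative ratio can mean cheaper and better or dearer and worse. A positive one can mean dearer and better or cheaper and worse. Ranking such values together and cutting off 2.5% at each end still prints two finite numbers, but they do not order the evidence and need not have 95% coverage.

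A non-inferiority trial planned around no difference is the setting where this is most likely. Cost-effectiveness is a named secondary aim, and the Background says that blended care has been expected to reduce costs. If the treatment proves merely non-inferior, the economic result may carry much of the case for adopting it.

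A separate, smaller matter is that the ICER's effect has no stated time point. The only HRSD-17 outcome labelled primary is the 3-month reduction, whereas the costs run to 12 months.

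**Working it through.** **Inputs** (Sample size section): margin 1.5 points = 0.31 SD, so SD = 1.5/0.31 = 4.84; one-sided α 0.025; power 80%; ρ = 0.5, so factor 1 − ρ² = 0.75; loss to follow-up 20%; 151 per arm.

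**Step 1: which true difference reproduces 151?** Normal approximation, zero true difference: n = 2 × [SD × (1.960 + 0.842)/1.5]².
- SD 4.84: n = 163.3; × 0.75 / 0.8 = 153.1.
- SD 4.8 (1.5/4.8 = 0.3125, which rounds to 0.31): n = 160.75; × 0.75 / 0.8 = 150.7, i.e. 151.
- True difference of 0.5 points against blended care: 345 per arm. The same in its favour: 87 per arm.

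Of the values tried, only zero fits.

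**Step 2: precision of the denominator.** Completers per arm = 0.8 × 151 = 120.8. SE = 4.84 × √0.75 × √(2/120.8) = 0.54 points (0.53 with SD 4.8 and 121 per arm). 95% half-width = 1.96 × 0.539 = 1.06 points.

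**Step 3: when is an interval for the ratio bounded?** The Fieller set holds all R with (ΔC − RΔE)² ≤ 1.96² × Var(ΔC − RΔE). As a quadratic in R its leading coefficient is ΔE² − 1.96² × SE². The set is bounded only if this is positive, that is, if the 95% interval for ΔE excludes zero. Costs do not enter this condition.

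The probability of a bounded interval is 1 − [Φ(1.96 − d/SE) − Φ(−1.96 − d/SE)], where d is the true difference:

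| True difference (points) | ρ 0.5, 20% loss (SE 0.54) | ρ 0, 20% loss (SE 0.62) | ρ 0.5, no loss (SE 0.48) |
|---|---|---|---|
| 0 | 5% | 5% | 5% |
| 0.5 | 15% | 13% | 18% |
| 1.0 | 46% | 36% | 55% |
| 1.5 | 79% | 67% | 88% |

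**Step 4: simulation of the bootstrapped denominator** (121 per arm, 1,000 replicates, two runs of 300 trials per scenario). At a true difference of zero, 92% to 94% of trials had more than 2.5% of replicates on each side of zero, with a median of about 23% on the minority side. At 0.5 points it was 80% to 81% of trials, and at 1.5 points about 21%.

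**Step 5: time points, side by side.**
- Costs: 12 months (Economic outcomes).
- ICER effect: the instrument is named, the time point is not (Economic outcomes).
- Response: defined at 3 and 12 months, so referring back to that definition does not settle it.
- Aims: short- and long-term cost-effectiveness are both listed (Study design and aims), but Economic outcomes describes only a 12-month horizon.
- TIC-P: at 3, 6 and 12 months in Table 1, but at 6 and 12 months with six-month recall under Direct and indirect costs. With that recall, a questionnaire at 3 months would reach about 3 months back before the start of follow-up.

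**The case against.** The strongest reply has five parts.

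- A zero difference is a sizing assumption, not a forecast. The Background describes antidepressants as ineffective in mild to moderate depression and psychological treatment as effective, and usual care is said to be mostly pharmacological. A real advantage is therefore possible. This stands, and it is why the size is given as a range. A reader might infer that the ratio interval is bound to be uninterpretable. The documents do not support that, since at 1.5 points most trials would give a bounded interval.
- The 95% figure is simply 1 − α under a true null and holds for a trial of any size. True. What is specific to this trial is that its own sample size points to that null, and that its precision leaves the problem common at 0.5 and 1.0 points.
- No bootstrap interval type is named, and the planned planes show which quadrant each replicate falls in. Both are true. The planes are appropriate, but the numerical statement of uncertainty remains an interval on the ratio. By the Fieller condition the difficulty lies in the ratio itself, not only in percentile limits.
- Net benefit and acceptability curves may appear in a fuller plan that is not shown. They may, and their absence is not the point. The point is that the article commits to intervals on the ratios.
- A reader might infer that the plan divides 12-month costs by a 3-month effect. The article does not say so. It names only the instrument, under a declared 12-month horizon, and a 12-month HRSD-17 exists. This is an ambiguity, not a stated mismatch.

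**Conclusion.** The concern holds in limited form. The article commits to bootstrap 95% intervals on the cost-effectiveness and cost-utility ratios. In the scenario that reproduces its sample size, the HRSD-17 denominator cannot be separated from zero in about 95% of trials, and an interval on the ratio then has no clear meaning. A bounded interval would be obtained in about 15%, 46% and 79% of trials at true differences of 0.5, 1.0 and 1.5 points.

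This rests on a zero planning difference, which is inferred, and on the 3-month design assumptions for SD, correlation and loss to follow-up. The documents give no variances for the 12-month HRSD-17, response or EQ-5D denominators. The figures at non-zero differences therefore do not carry over to those ratios, and the 5% figure does so only if their true differences are also zero.

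The time point of the ICER effect is unspecified and needs stating. Both matters concern a secondary, economic analysis.

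**What to change.** Replace the sentence on ratio intervals. From the same bootstrap samples, report incremental net monetary benefit with 95% intervals over a stated willingness-to-pay range, together with acceptability curves and the planned planes. Give the ICER as a point estimate only.

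Add one sentence stating that 12-month HRSD-17, 12-month response and 12-month QALYs are paired with the 12-month costs.

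These changes need no new data: the HRSD-17 and EQ-5D are already scheduled at 12 months. The small cost is that a willingness-to-pay range has to be chosen in advance for each effect measure.

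A 3-month cost-effectiveness analysis for the short-term aim is a different matter. It first requires reconciling the TIC-P schedule in Table 1 with the section on direct and indirect costs. If there is no 3-month TIC-P, or if its recall stays at six months, the 3-month costs cannot be obtained by rewording alone.

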## Discussion

There is a need to investigate accessible ways to offer psychological treatment in general practice as both GPs and patients prefer psychological treatment [21–23]. However, barriers to psychological treatment in general practice such as time constraints and lack of experience of the GP (28–30), result in GPs prescribing pharmacological treatment even as a first step [76]. This contrasts sharply with the guidelines recommending non-pharmacological treatment as the first step [12, 13] and is unwanted in view of the side effects, poor adherence, and long-term use after remission associated with antidepressant use [77–79]. Blended care interventions may provide GPs a feasible instrument to offer structured psychological treatment.

The current paper presents the design of a pragmatic non-inferiority trial to study the effectiveness and cost-effectiveness of a blended behavioral activation treatment for depressive symptoms and disorders in general practice.

While previous studies mainly used online psychological interventions based on cognitive behavioral therapy (CBT) [28, 32, 80], behavioral activation has been shown as effective and more cost-effective compared to CBT(50). In addition, it has been experienced as less complicated and more accessible to patients and therapists [81]. MHWs can learn the technique required quickly and its effectiveness is comparable to behavioral activation delivered by more specialist staff with more training [49]. It is expected that blended behavioral activation will provide an accessible and easier way to provide psychological treatment in general practice.

To our knowledge, this is the first trial of blended care based on behavioral activation in general practice provided by patients’ own GP or MHWs including assessments of real-time experiences during treatment by the EMA. An important strength of this trial is that it is conducted in routine general practice. Patients are recruited and coached by their own GPs and MHWs during treatment, hereby mirroring routine general practice and increasing the study’s generalizability. Another strength is that the EMA has the advantage of reducing memory distortions compared to conventional questionnaires. It gives insight into actual experiences during treatment [82]. In future, knowledge of patients’ real-time experiences may enable the development of more personalized blended care for depression [65]. This randomized controlled trial will show whether a blended behavioral activation treatment is a non-inferior treatment strategy for patients with depressive symptoms and depressive disorder in general practice.

## Abbreviations

CAU: Care as usual
CBT: Cognitive behavioral therapy
EMA: Ecological Momentary Assessments
EQ-5D: EuroQol five dimensions questionnaire
FDA: Federal Drug Administration
GP: General practitioner
HRSD-17: Hamilton Rating Scale for Depression, 17 items
ICER: Incremental Cost-Effectiveness Ratio
ICF: International Classification of Functioning, Disability and health
ITT: Intention To Treat
MHW: Mental health worker
QIDS-16: Quick inventory of depressive symptomatology, 16 items
SCID: Structured Clinical Interview for DSM disorders
TIC-P: Trimbos and iMTA questionnaire on Costs associated with Psychiatric illness
VAS: Visual analogue scale
WHODAS-II: WHO Disability Schedule 2.0; EQ-5D
